## Methods and analysis

### Study design

The study (also known as the SPRINT study (The Prevalence of Social Communication PRoblems in Adult Psychiatric InpaTients)) will employ a multiple-phase cross-sectional design for participants without ID, and a single-phase design for participants with ID (figure 1). A multiple-phase approach to studying ASD prevalence has been used in several previous similar studies,^12 19 39^ as the ASD clinical interview-based diagnostic assessments are both time and resource intensive.^40^ Thus, a multiphase approach permits coverage of a larger study population per unit of resource. However, such an approach is heavily reliant on the accuracy of the tool used in the first phase in identifying probable cases of ASD.

**Figure 1 F1:**
[figure not shown]
Flow chart summary of study design. ASDs, Autism spectrum disorders; AQ, autism quotient

In terms of the multiple-phase design for non-ID patients, transition to Phase II will be selected via stratified random sampling according to the patient’s scores on the Autism Quotient (AQ)^41^ questionnaire (table 1). This weighted approach enables generation of a prevalence estimate for the population as a whole (compared with if there were a single threshold AQ score for Phase II progression) and has been extensively validated, including in the 2014 APMS.^13^

**Table 1 T1:** The probability of selection for Phase II according to total scores in the AQ questionnaire. This probability framework has been validated in a previous study conducted on adult participants from a mixture of inpatient and community mental health settings.^39^ Participants scoring higher on these questionnaires will have a greater probability of selection

AQ score	Probability of selection
≤19	0.1
20–24	0.2
25–29	0.3
30–39	0.6
≥40	1.0

The rationale for a single-phase design in patients with ID is twofold. First, there is a lack of validated and relevant ASD questionnaires for this patient group.^42^ Second, the prevalence of ASD in this patient group is substantially higher in community studies,^12^ such that a single-phase design would be less resource-inefficient in identifying individuals meeting ASD diagnostic criteria within this group.

### Study population

The total sample will comprise 200 patients between the ages of 18 and 65 years, with a history of having been a psychiatric inpatient on an adult acute mental health ward during the study time period (from 6 March 2019 to 31 December 2020). The inclusion and exclusion criteria are summarised in table 2. Out of these 200 patients undergoing Phase I testing, 40 will transition to Phase II of the study. The Phase II patient group will consist of 25±5 non-ID patients, and 15±5 patients with ID.

**Table 2 T2:** Inclusion and exclusion criteria. Additionally, participants lacking capacity will be withdrawn from the study if they become distressed by the assessment process and/or their guardians are not in agreement with them remaining in the study

Inclusion criteria	Exclusion criteria
Aged between 18 and 65 years.	<18 or >65 years of age.
Being or having been a psychiatric inpatient on an adult acute mental health ward during the study time period.	Having no history of being a psychiatric inpatient on an adult acute mental health ward during the study time period.
	Clinical diagnosis of dementia.
	Not understanding written and/or verbal English.

Study participants will be recruited from two inpatient units based in Leicestershire, UK. These units serve a population of approximately 1 million people living in both urban and rural areas within Leicester, Leicestershire and Rutland.^43^ Applications to extend the study to further sites are currently in progress.

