**Methods and analysis:**

A multiple-phase approach will be used. Phase I will involve testing of 200 patients and corresponding informants, using the autism quotient (AQ), the informant version of the Social Responsiveness Scale, second edition—Adult, the self and informant versions of the Adult Social Behaviour Questionnaire and the EuroQol-5D-5L. Patients with intellectual disability (ID) will bypass Phase I.

Phase II will involve diagnostic testing of a subgroup of 40 patients with the Diagnostic Interview for Social and Communication Disorders, the Autism Diagnostic Observation Schedule version 2 and the ASD interview within the Schedules for Clinical Assessment in Neuropsychiatry version 3. 25±5 patients will not have ID and be selected via stratified random sampling according to AQ score; 15±5 patients will have ID. Phase II patients will be interviewed with the Physical Health Conditions and Mental Illness Diagnoses and Treatment sections of the 2014 Adult Psychiatric Morbidity Survey.

Prevalence estimates will be based on the proportion of Phase II participants who satisfy the 10th revision of the International Statistical Classification of Diseases and Related Health Problems Diagnostic Criteria for Research (ICD-10-DCR) and the 5th edition of the Diagnostic and Statistical Manual of Mental Disorders (DSM-5) diagnostic criteria for ASD, adjusting for selection and non-response. Univariate analysis will be conducted for comorbidities to identify the level of their association with an ASD diagnosis.

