### Measures

The measures to be used are summarised in table 3. The Phase I measures, which will be used to test non-ID participants only, include the AQ,^41^ which is recommended by the National Institute for Health and Care Excellence as referral tools for adults with possible ASD who do not have ID.^44^ Also included in the test battery are ASD tools which are less comprehensively validated in adult populations, but appear to show promise, including the Informant version of the Social Responsiveness Scale, second edition^45^ and the Self-report and Informant versions of the Adult Social Behaviour Questionnaire, ASBQ.^46^ Phase I also includes a basic information form for participants, including demographic details, encompassing basic demographic information and information pertaining to mental and physical health, including the 2014 APMS mental illness and physical health conditions checklists, thus enabling measurement harmonisation and wider comparison.^13^ Additionally, both participants and informants will complete the EuroQol-5D-5L,^47^ a self-report instrument that measures general health.

**Table 3 T3:** Summary of study measures

Measure	Purpose
**Phase** **I** (non-ID participants only)	
Autism Quotient, AQ^41^	Measuring likelihood of ASD.
Informant version of the Social Responsiveness Scale, second edition, SRS-A^45^	
Self-report and Informant versions of the Adult Social Behaviour Questionnaire, ASBQ^46^	
Self-report and Informant versions of the EuroQol-5D-5L, EQ-5D-5L^47^	Measuring quality of life.
Basic information form	Collecting information pertaining to patient demographics, as well as the 2014 Adult Psychiatric Morbidity Survey (APMS) mental illness and physical health conditions checklists.^13^

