### Data analysis plan

The primary outcome parameter will be based on patients who transition to Phase II of the study. The ASD prevalence estimate will be calculated based on the proportion of Phase II participants who meet the ICD-10-DCR and DSM-5 diagnostic criteria for ASD on clinical assessment, with adjustment for selection and non-response, as well as the different study designs for the ID and non-ID patient subgroups.

For the feasibility study, the analyses will be descriptive. For continuous variables, values and SD will be reported; for categorical variables, percentages and SD will be reported. We will use multiple imputation to account for any missing data. For the full-powered study, the generalised linear model will be used to estimate the difference between groups, as well as corresponding OR, 95% CI and p values.

The analyses will be primarily conducted in SPSS (version 26), but for more advanced statistical analyses (such as use of the generalised linear model) and graphical representation, we will use R.

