### Sample size justification

The sample size was calculated with direct statistician support, as well as the use of a statistical textbook and related software.^51^ For a significance level of 0.05 and power of 85%, assuming estimates of 1% community ASD prevalence and 5% inpatient ASD prevalence,^15^ a sample size of 374 patients is required. Ideally, we would be subjecting a minimum of 374 patients to Phase II testing. This is because only participants completing Phase II interview assessments will yield data pertaining to the primary outcome variable (ie, the presence or absence of satisfying diagnostic criteria for ASD).

However, in the first instance, around 40 patients (from the minimum of 200 subjected to Phase I testing) will be selected for Phase II testing (via stratified random sampling for non-ID patients, whereas ID patients will progress automatically to Phase II). The Phase I sample size of 200 patients takes into account the probability sampling method for Phase II selection, in addition to allowing for losses to follow-up for Phase I participants invited for Phase II testing. Our results will assume that the data for these 40 patients are representative of the larger group subjected to Phase I testing. Owing to the sample size, the SPRINT study shou

ld be considered a pilot/feasibility study, the intention of which being to establish and further refine the technical, administrative and logistical aspects of the study, with a view towards sample size expansion on its completion. The sample size represents an appropriate sample size for a feasibility study of this type.^52 53^

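### The article counts patients with intellectual disability (ID) both inside and outside the 200 Phase I patients, so the 40 in Phase II cannot represent the Phase I group and the ID weight in the overall prevalence needs a stated source

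*Protocol article*

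**What the plan says.** On the size and make-up of the sample, the article says:

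- Study population: "The total sample will comprise 200 patients between the ages of 18 and 65 years". It continues: "Out of these 200 patients undergoing Phase I testing, 40 will transition to Phase II of the study". It then divides the 40: "The Phase II patient group will consist of 25±5 non-ID patients, and 15±5 patients with ID".
- Sample size justification: "around 40 patients (from the minimum of 200 subjected to Phase I testing) will be selected for Phase II testing". The same sentence adds "whereas ID patients will progress automatically to Phase II". Here 200 is a minimum for Phase I; in Study population it is the total.
- Abstract, Methods and analysis: "Patients with intellectual disability (ID) will bypass Phase I".
- Measures: "The Phase I measures, which will be used to test non-ID participants only". Table 3 repeats the restriction, and Study design gives ID patients a single-phase route.

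On the estimate, the Data analysis plan promises adjustment for selection and non-response, "as well as the different study designs for the ID and non-ID patient subgroups". The Sample size section, however, states as an assumption of the results that the 40 can stand for everyone tested in Phase I.

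**The concern.** The statements about who is in the 200 cannot all be true. Patients who never enter Phase I cannot be among those who move on from it.

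This reaches the primary outcome in two ways. First, the representativeness assumption ties the 40 to a group that contains no ID patients, although more than a third of the 40 are meant to have ID. Second, an overall prevalence has to combine an ID estimate and a non-ID estimate. Table 1 supplies weights within the non-ID group only. Joining the two groups also needs the proportion of eligible inpatients who have ID, and the article names no source for it. If the recruited counts were used, and 15±5 is a target rather than what recruitment naturally yields, the target would influence the headline figure.

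**Working it through.** **The article's own figures.** 25 + 15 = 40, with a range of 20 + 10 = 30 to 30 + 20 = 50. The split of Phase II adds up. The conflict is over where the 15 come from.

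**Two readings of the 200.**

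| Reading | Non-ID in Phase I | ID | Total | ID share of those enrolled |
|---|---|---|---|---|
| ID inside the 200 | 190 / 185 / 180 | 10 / 15 / 20 | 200 | 5.0% / 7.5% / 10.0% |
| ID outside the 200 | 200 | 10 / 15 / 20 | 210 / 215 / 220 | 4.8% / 7.0% / 9.1% |

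Under either reading, 25±5 rather than 40 move from Phase I to Phase II. Table 1 does not settle which is meant. With the lowest selection probability of 0.1 for everyone, at least 0.1 × 200 = 20 or 0.1 × 185 = 18.5 non-ID patients would be selected, and both are compatible with 25±5 once higher scores and losses are allowed for.

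**Representativeness.** ID share in Phase II: 15/40 = 37.5%. ID share in Phase I: 0. Within the non-ID group, Table 1 selects with probabilities from 0.1 to 1.0, so those patients also represent Phase I only after weighting.

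**Effect of the ID share on the overall prevalence.** Let s be the ID share:

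overall = (1 − s) × P(non-ID) + s × P(ID)

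Assumptions: P(non-ID) = 2.6%, which is not in the article. P(ID) = 1%, the Introduction's community figure for mild ID; 20%, an intermediate value; or 38%, between its 35.2% and 42.3% for women and men with moderate to profound ID. The article does not give the true share; 2% is included only as a lower illustration.

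| s | P(ID) = 1% | P(ID) = 20% | P(ID) = 38% |
|---|---|---|---|
| 2% | 2.57% | 2.9% | 3.3% |
| 5% (10 of 200) | 2.52% | 3.5% | 4.4% |
| 10% (20 of 200) | 2.44% | 4.3% | 6.1% |
| 37.5% (15 of 40, no adjustment) | 2.0% | 9.1% | 15.9% |

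Example: 0.95 × 0.026 + 0.05 × 0.38 = 0.0437, and 0.90 × 0.026 + 0.10 × 0.38 = 0.0614.

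The change from 5% to 10% is 0.05 × (P(ID) − P(non-ID)):
- P(ID) = 20%: 0.05 × 0.174 = 0.9 points
- P(ID) = 38%: 0.05 × 0.354 = 1.8 points
- P(ID) = 1%: 0.05 × (−0.016) = −0.08 points

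**Sensitivity to the non-ID assumption.** With P(non-ID) = 5%, the article's planning value for inpatients, moving from a 5% to a 10% share takes the overall figure from 5.75% to 6.5% at P(ID) = 20% and from 6.75% to 8.5% at P(ID) = 40%. At P(ID) = 1% it goes from 4.8% to 4.6%. The pattern is the same.

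**Inside versus outside the 200.** At 20 ID patients the shares are 10.0% and 9.1%. With P(non-ID) = 2.6% and P(ID) = 38%, the difference is 0.0091 × 0.354 = 0.3 points. At 15 ID patients it is 0.0052 × 0.354 = 0.2 points.

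**The case against.** A reader might infer that the overall prevalence is set by a recruitment quota. The documents do not support that as a statement of fact.

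- No section says the recruited ratio will be the weight. The Data analysis plan commits to adjusting for the two designs. The source of the weights may be given in the full protocol or analysis plan, which are not shown.
- The word quota is itself an inference. The same ± notation is used for non-ID patients, whose number results from Table 1 and losses, and ID patients progress automatically. So 15±5 may be an expected yield. If ID patients are enrolled as they occur, the recruited share would estimate the inpatient share.
- The 9.1% to 15.9% range describes an unadjusted analysis, which the Data analysis plan rules out.
- If the ID inpatients mostly have mild ID, the share hardly matters.
- This is a pilot with descriptive analyses. One case in the lowest AQ stratum carries weight 1/0.1 = 10, or 10/200 = 5 points, more than the share effect shown here.

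All of this limits the weighting concern to a conditional one. It does not remove the contradiction in the counts or rescue the representativeness sentence. Nor does the article state consecutive recruitment, which is what would make the recruited ratio a fair estimate of the share. Sampling noise from a large weight shows in a confidence interval; a wrong ID share does not.

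**Conclusion.** Two things are wrong as written. The 40 cannot all come from 200 patients tested in Phase I, and the 40 cannot be taken as representative of a Phase I group without ID patients. The second also conflicts with the adjustment promised in the Data analysis plan. Both should be corrected, but they do not undermine the study: choosing between about 215 in total and about 185 in Phase I moves the overall prevalence by about 0.3 points or less.

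The larger effect is conditional. It needs weights taken from recruited counts, a 15±5 that is a target rather than a natural yield, and clearly higher ASD prevalence in ID than in non-ID inpatients. If all three hold, a 5% versus a 10% ID share moves the overall figure by 0.9 to 1.8 points, with non-ID prevalence assumed at 2.6% and ID prevalence at 20% to 38%. At 1% ID prevalence the movement is under 0.1 point. The article gives neither the inpatient ID share nor the severity mix, so no single corrected prevalence can be calculated.

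**What to change.** 1. State one set of numbers throughout. Either 200 non-ID patients in Phase I, of whom 25±5 complete Phase II, plus 15±5 ID patients entering Phase II directly (about 215 in total); or 200 in total, with about 185 in Phase I. Say whether 15±5 is a target or an expected yield.
2. Delete or correct the representativeness sentence in Sample size justification. It can apply only to the non-ID Phase II patients, and only after Table 1 weighting.
3. Count eligible ID and non-ID inpatients on the two units during recruitment.
4. Combine the Table 1-weighted non-ID estimate with the ID estimate using that counted share, not the recruited ratio.
5. Report the ID and non-ID estimates alongside the combined one. The design already allows the two groups to be considered separately.

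The cost is a change of wording and a small screening-log burden on two units. No extra patients are needed. The count is easier to keep during recruitment than to reconstruct afterwards.

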### Patient and public involvement

The study design was refined following consultation group sessions with both patients with ID and their carers, as well as patients without ID and their carers. Significant changes made to the study design were made as a result of these sessions, including reduction of the questionnaire and interview burden, as well as incorporation of a stigma measure for patients with ID, as this was considered a research priority by patients with ID and their carers.

Patients and carers will all receive a report summarising the findings of the study, unless they request not to, and an easy-read version of the report will be developed for patients with ID.

### Measures

The measures to be used are summarised in table 3. The Phase I measures, which will be used to test non-ID participants only, include the AQ,^41^ which is recommended by the National Institute for Health and Care Excellence as referral tools for adults with possible ASD who do not have ID.^44^ Also included in the test battery are ASD tools which are less comprehensively validated in adult populations, but appear to show promise, including the Informant version of the Social Responsiveness Scale, second edition^45^ and the Self-report and Informant versions of the Adult Social Behaviour Questionnaire, ASBQ.^46^ Phase I also includes a basic information form for participants, including demographic details, encompassing basic demographic information and information pertaining to mental and physical health, including the 2014 APMS mental illness and physical health conditions checklists, thus enabling measurement harmonisation and wider comparison.^13^ Additionally, both participants and informants will complete the EuroQol-5D-5L,^47^ a self-report instrument that measures general health.

**Table 3 T3:** Summary of study measures

Measure	Purpose
**Phase** **I** (non-ID participants only)	
Autism Quotient, AQ^41^	Measuring likelihood of ASD.
Informant version of the Social Responsiveness Scale, second edition, SRS-A^45^	
Self-report and Informant versions of the Adult Social Behaviour Questionnaire, ASBQ^46^	
Self-report and Informant versions of the EuroQol-5D-5L, EQ-5D-5L^47^	Measuring quality of life.
Basic information form	Collecting information pertaining to patient demographics, as well as the 2014 Adult Psychiatric Morbidity Survey (APMS) mental illness and physical health conditions checklists.^13^
**Phase I** **I**	
Diagnostic Interview for Social and Communication Disorders, DISCO^48^	Establishing whether participant meets diagnostic criteria for ASDs.
Autism Diagnostic Observation Schedule version 2, ADOS-2^49^	
The Mental Illness Diagnoses and Treatment section of the 2014 APMS^13^	Establishing participant’s psychiatric and physical health comorbidities.
The Physical Health Conditions section of the 2014 APMS^13^	
ASD interview subsection of version 3 of the Schedules for Clinical Assessment in Neuropsychiatry, ASD-SCAN-3	Field testing of interview schedule (for non-ID participants only).
Stigma Questionnaire for people with Intellectual Disability, SQID^50^	Participants experience of stigma (for ID participants only).
Basic information form	Collecting information pertaining to patient demographics, as well as the 2014 Adult Psychiatric Morbidity Survey (APMS) mental illness and physical health conditions checklists^13^ (for ID participants only, as this form is completed in phase I for non-ID participants).

ID, intellectual disability.

The Phase II measures include the DISCO^48^ (although the interview will be limited to the diagnostic algorithm, psychiatric conditions and forensic problems items) and ADOS-2,^49^ both of which are tools with established validity for the diagnosis of ASDs. Also, psychiatric and physical comorbidities will be assessed using the relevant sections of the 2014 APMS interview.^13^ Other tests include the field testing of the ASD interview of version 3 of the Schedules for Clinical Assessment in Neuropsychiatry, as well as the Stigma Questionnaire for people with Intellectual Disability.^50^

### Outcome parameters

The primary outcome parameter for this pilot study is the presence or absence of meeting ICD-10-DCR and DSM-5 diagnostic criteria for ASDs, respectively. Secondary outcome parameters, including the study phase in which the corresponding parameters are collected, are summarised in table 4.

**Table 4 T4:** Summary of secondary outcome parameters

Outcome category	Corresponding parameters	Study phase in which data is collected
Autism questionnaire data	Autism Quotient, AQ^41^ Informant version of the Social Responsiveness Scale, second edition, SRS-A^45^ Self-report and Informant versions of the Adult Social Behaviour Questionnaire, ASBQ^46^	Phase I
Basic demographic information	Date of birth Sex Postcode Ethnic group Employment status Relationship status	Phase I (non-ID participants) Phase II (ID participants)
Mental health history	Date of most recent psychiatric hospital admission Discharge date of most recent psychiatric hospital admission (where applicable) Total number of inpatient psychiatric admissions 2014 Adult Psychiatric Morbidity Survey (APMS) mental illness checklist^13^	Phase I (non-ID participants) Phase II (ID participants)
	The Mental Illness Diagnoses and Treatment section of the 2014 APMS^13^	Phase II
Physical health history	2014 APMS physical health conditions checklist^13^	Phase I (non-ID participants) Phase 2 (ID participants)
	The Physical Health Conditions section of the 2014 APMS^13^	Phase II
General health	EuroQol-5D-5L^47^ data for participants and informants	Phase I
Stigma experience (ID participants only)	Stigma Questionnaire for people with Intellectual Disability, SQID^50^	Phase II (ID participants)

ID, intellectual disability.

